#### **12.4.2. Definition of source data**

Source documents are original records in which raw data are first recorded. These may include, e.g. hospital/clinic/general practitioner records, charts, diaries, laboratory results, printouts, pharmacy records, care records, ECG or other printouts. Source documents will be kept in a secure, limited access area.

Some data will be recorded directly in the CRF and will not appear in a source document as defined in the Source Data Location Sheet (e.g. BMI, BP, waist-hip ratio).

Source documents that are computer-generated and stored electronically will if possible/practical be printed for review by the monitor. Once printed, these copies will be signed and dated by the Scientific Lead or CI where appropriate and become a permanent part of the subject's source documents.

The Scientific Lead will authorize the monitor to compare the content of the print out and the data stored in the computer to ensure all data are consistent. If electronically stored and impractical to print, each timely review of the electronically-stored data will be annotated in the patient's notes.

#### **12.4.3. Source data verification**

Source data verification ensures accuracy and credibility of the data obtained. During monitoring, reported data are reviewed with regard to being accurate, complete, and verifiable from source documents (e.g. subject files, recordings from automated instruments, ECG tracings, laboratory notes). All data reported on the CRF will be supported by source documents, unless otherwise specified in section 12.4.2. Data Verification and will be carried out by the Scientific Lead and members of the study team who will check the CRF for completeness and clarity, and crosscheck them with source documents.

#### **12.4.4. Quality assurance**

Investigators will promptly notify the Sponsor Quality Assurance Office of the following within the required timeframe:

- Serious breaches of GCP
- Urgent safety measures
- Protocol violations
- Any amendments to the trial
- Any changes the Clinical Trial Risk Assessment (form A).
- Any other issues as stated in the study contract or agreement

#### **12.4.5. Trial oversight**

#### **12.4.6. Data monitoring, ethics and trial steering committee**

Independent oversight of the study will be conducted by the Independent Data Monitoring, Ethics and Trial Steering Committee. Amongst its members will be an independent chair, a lay individual (from the Leeds Musculoskeletal Biomedical Research Unit Public and Patient Advocacy Group), a clinician who is independent of the study research team, and a representative of the LIRMM study management group. They are expected to meet at least quarterly. A copy of the Independent Data Monitoring, Ethics and Trial Steering Committee minutes will be forwarded to the Sponsor QA office for review.

The daily running of the trial will be co-ordinated by [name] who will lead the Trial Management Group (also comprising of [name], [name] and [name]).

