## **7. STUDY BLINDING**

### **7.1. Type of blinding**

Treatment groups will be allocated in a double-blind manner. Participants will be blinded to the treatment they receive (placebo or IMP) throughout all stages of the study. Investigators will also be blinded to the treatment until all samples have been collected and processed. Blinding will be generated by the dedicated trials pharmacy representative who has signed/dated the staff delegation log and is not otherwise associated with this study.

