## **13.8. Planned interim analysis and data monitoring**

In this small study with short follow-up no formal interim efficacy analysis is planned. Data monitoring will be carried out during the trial by the study management team and the sponsor (see section 12.4). . Interim safety monitoring will be conducted by the study Data Management and Ethics Committee. The DMEC independent statistician will obtain the randomisation list from pharmacy and will code this as treatment A or B before passing to the trial statistician. The trial statistician will produce both open (blinded) and closed

(unblinded) reports for the DMEC, the latter using the treatment codes. Only safety data values will be presented by treatment group; data completeness will be summarised for all secondary variables and for biopsy success. Feasibility data will also be presented. The primary outcome will not be available for interim analysis as this will not be calculated until after the final patient completes follow-up. The trial statistician will not be present when closed reports are discussed by the DMEC with knowledge of the codebreak, which will be supplied to committee members by the DMEC independent statistician. The DMEC will examine at least one set of interim safety data after the first 8 patients have completed the trial up to day 35 (or have been withdrawn); timings of subsequent analyses will be informed by the findings of the first analysis.

There will be a blind review of the data after the last patient has completed follow-up.

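### Sections 12.4.6 and 13.8 together leave a route by which a study management group representative could receive closed safety reports and the codebreak while the trial is running

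*Protocol*

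**What the plan says.** **Oversight (protocol 12.4.6).** "Independent oversight of the study will be conducted by the Independent Data Monitoring, Ethics and Trial Steering Committee". The members mentioned are an independent chair, a lay person, a clinician from outside the research team and "a representative of the LIRMM study management group". The list is introduced as a partial one, and no limit is placed on what any member may see. The committee is to meet at least quarterly, and its minutes go to the sponsor's quality assurance office. The section then names, separately, the group that runs the trial day to day.

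**Interim safety review (protocol 13.8).** "Interim safety monitoring will be conducted by the study Data Management and Ethics Committee". That committee's independent statistician obtains the randomisation list from pharmacy, codes it A or B and passes it to the trial statistician, who prepares an open blinded report and a closed unblinded one. The trial statistician stays out of the discussion held with knowledge of "the codebreak, which will be supplied to committee members by the DMEC independent statistician". At least one set of safety data is reviewed, after the first 8 patients have reached day 35 or been withdrawn. Only safety values are shown by arm, and the primary outcome is not available.

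**Blinding (protocol 7.1 and 6.4.3).** Section 7.1: "Investigators will also be blinded to the treatment until all samples have been collected and processed". Section 6.4.3 gives access to the randomisation schedule to the trials pharmacy alone until sample collection is complete.

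**The concern.** A representative of study management is ordinary on a steering committee. The difficulty is that 12.4.6 merges steering with data monitoring, while 13.8 hands the codebreak to the committee's members without exception. The authors of 13.8 saw the need for a barrier, since they keep the trial statistician out of the unblinded discussion, but they apply it to nobody else.

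Several assessments in this trial depend on the blind being kept. The Scientific Lead takes the sudomotor, hydration, water-loss and tape-stripping measurements (9.2.3.1 to 9.2.3.4) and makes the first judgement of whether a serious event is related to treatment (11.6.2). A panel including clinical study team members decides who enters the per-protocol set before unblinding (13.6). If knowledge of the arms behind the safety tables reached any of these people, it could colour those judgements. Section 9.1 holds the primary-assay samples frozen precisely to avoid accidental unblinding; the committee route has no comparable safeguard.

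**Working it through.** This is a comparison of text. The only arithmetic is the timing of the first review.

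1. **Is a member tied to the study listed on the committee?** Yes. Section 12.4.6 lists the study management group representative and attaches no restriction to that seat.

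2. **Who receives the codebreak?** Section 13.8 says committee members, with no exception. The one stated absence is the trial statistician, and that is from the discussion of closed reports.

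3. **Are the committees in 12.4.6 and 13.8 the same body?** Probably, but this is not stated. Section 12.4.6 constitutes the only committee with a data monitoring and ethics remit. Section 13.8 uses a different name, and 12.5.2 refers to a Data Management Committee. The cross-reference in 13.8 to section 12.4 concerns monitoring by the study management team and the sponsor, so it does not settle the question.
   - If they are the same body, the representative falls within the group that is given the codebreak.
   - If they are different bodies, the committee that is given the codebreak has no stated membership.
   - Either way the text needs correction.

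4. **Is the representative one of the blinded investigators of 7.1?** Not stated. Section 12.4.6 does not equate the LIRMM study management group with the group that runs the trial, and no section gives this representative an assessment role.

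5. **When, and how much?** First review: 8 / 30 = 0.267, or 27% of the planned sample, so the trial is still under way. By-arm content is safety data only. One review is fixed; the timing of any later one depends on the first. The quarterly frequency in 12.4.6 refers to meetings and does not fix a number of closed sessions.

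6. **What does the codebreak reveal?** It turns A and B into named arms in the closed report and in any later report that uses the same codes. The patient-level coded list goes to the trial statistician, who is kept out of the codebreak discussion. Only the independent statistician is described as holding both, and members are not said to receive individual allocations.

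7. **Does 6.4.3 fit with 13.8?** No. Under 6.4.3 only pharmacy can access the schedule until all samples are collected. Under 13.8 the independent statistician obtains the list in time for a review after 8 patients, when later patients still have samples to give. The release in 13.8 is a sensible arrangement, but 6.4.3 as written does not permit it.

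**The case against.** The strongest reply is that no breach of the blind is written into the protocol. Section 13.8 provides separate open and closed reports, A/B coding and a codebreak held by an independent statistician. It also distinguishes data monitoring by the study management team from safety monitoring by the committee. Attendance at closed sessions is commonly left to a committee charter. The by-arm content is limited to safety, the steroid extraction and counting behind the primary variable are done only at the end of the trial, and the analysis is descriptive throughout (13.2).

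Much of this stands, and it rules out several readings that a reader might be tempted to make:

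- **That allocation does reach the blinded trial team.** This needs the two committees to be one, the representative to belong to the blinded team, and the representative to attend the closed part or pass information on. The protocol states none of these.
- **That the committee is independent only in name.** The chair and one clinician are stated to be independent, and there is a lay member.
- **That the committee lacks a statistician.** The membership list is not exhaustive, and 13.8 refers to an independent statistician.
- **That several closed sessions will take place.** Only one is fixed.
- **That members learn each patient's arm.** The codebreak is described at group level.

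The charter argument does not dispose of the point. This protocol does not leave the matter open: it states who sits on the committee and who is given the codebreak, and it names one person who must be absent. Followed literally, those statements admit a non-independent member. A charter that excluded that member would depart from the protocol's wording.

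**Conclusion.** The point holds as an open route to unblinding. It does not hold as a statement that unblinding occurs. It rests on the likely but unstated assumption that 12.4.6 and 13.8 describe one committee. If that assumption fails, the remaining defect is that the body receiving the codebreak has no defined membership.

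The size is modest. One closed review is certain, at 27% of the planned sample, with only safety data by arm and no primary outcome. Any effect would depend on information passing to those who take the skin measurements, judge causality or allocate the per-protocol set, and the documents give no basis for estimating how likely that is. The mismatch between 6.4.3 and 13.8 on access to the randomisation schedule needs no such assumption. Both should be corrected before the first closed report is prepared, because the change alters a stated rule on who may see unblinded material and costs very little.

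**What to change.** - Use one committee name in 12.4.6 and 13.8, and make clear whether the Data Management Committee in 12.5.2 is the same body.
- State in 12.4.6 and 13.8 that closed reports, closed minutes and the codebreak go only to members independent of the study team, and that the study management representative attends open sessions only.
- Keep closed minutes apart from those forwarded to the sponsor's quality assurance office. Section 11.6.3 already leaves out confidential reports and minutes when material is shared with the drug supplier.
- Amend 6.4.3 to permit the release of the randomisation list to the independent statistician that 13.8 describes.

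The cost is a few sentences in the protocol and matching wording in any committee charter. No new staff are needed, since 13.8 already provides for the independent statistician, and the analyses and review timing do not change.

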## 12.5. Data handling

### 12.5.1. CRF completion

The research team is responsible for prompt reporting of accurate, complete, and legible data in the CRFs and in all required reports. Any change or correction to the paper CRF will be dated, initialled, and explained (if necessary) and will not obscure the original entry. Use of correction fluid is not permitted. The Scientific Lead will maintain a list of personnel authorized to enter data into the CRF. Detailed instructions will be provided in the CRF Instructions.

### 12.5.2. Database entry and reconciliation

CRF/external electronic data will be captured on an electronic spreadsheet, accessible only to the CI and delegated personnel and stored on a secure server with regular backups. Periodic manual reviews will be conducted to check for discrepancies and to ensure consistency with CRF/external electronic data. Upon completion, the database will be locked for editing and subjected to final data inspection as recommended by the Data Management Committee before analysis.

### 12.5.3. Screening and enrolment logs

Subject's Screening will be recorded in the Subject Screening Log.

The Scientific Lead will keep a list containing all subjects enrolled into the study. This list remains with the Scientific Lead and is used for unambiguous identification of each subject. The list contains the subject identification number, full name, date informed consent signed and the hospital number or National Health Security number, if applicable.

The subject's consent and enrolment in the study must be recorded in the subject's medical record. These data will identify the study and document the dates of the subject's participation.

## 12.6. Archiving and data retention

In line with the principles of GCP/UK Clinical Trial Regulations, at the end of the trial, essential documents will be securely archived at each participating centre for a minimum of 15 years. However, because of international regulatory requirements, the Sponsor may request retention for a longer period. Arrangements for confidential destruction will then be made. **If a patient withdraws consent for their data to be used, it will be confidentially destroyed immediately.** No records/study documentation/data may be destroyed without first obtaining written permission from the Sponsor.

Essential documents include (this list is not exhaustive):

- Signed informed consent documents for all subjects
- Subject identification code list\*, screening and enrolment log

- Record of all communications between the CI, the REC and the Sponsor
- Composition of the REC, and the Sponsor (or other applicable statement as described in section 14.6).
- List of sub-Investigators and other appropriately qualified persons to whom the Scientific Lead/CI has delegated significant trial-related duties, together with their roles in the study and their signatures
- Copies of CRF and documentation of corrections for all subjects
- Investigational product accountability records
- Record of any body fluids or tissue samples retained
- All other source documents (subject medical records, hospital records, laboratory records, etc.)
- All other documents as listed in section 8 of the ICH E6 Guideline for GCP (Essential Documents for the Conduct of a Clinical Trial)

\*European Union legislation requires this list to be maintained for a minimum of 15 years.

Normally, these records will be held in the Scientific Lead's archives. If the Scientific Lead is unable to meet this obligation, he or she must ask the Sponsor for permission to make alternative arrangements. Details of these arrangements will be documented.

## **12.7. Study suspension, termination and completion**

Suspension or termination of the study may occur at any time for any reason, following discussion between the Investigators and the Sponsor. In the case of early study termination the Sponsor or Sponsor-delegated individual will be responsible for completing a premature end of study report to the MHRA and the REC within 15 days. Upon study completion, the Sponsor or Sponsor-delegated individual will be responsible for sending the Declaration of the End of a Clinical Trial to the MHRA within 90 days. The Sponsor or Sponsor-delegated individual will be responsible for providing the end of trial report to the MHRA within 1 year of the end of the trial.

## **13. DATA EVALUATION**

### **13.1. Responsibilities**

Data analysis, report preparation and study dissemination will be conducted by the Scientific Lead and other delegated authorised personnel.

### **13.2. Hypotheses**

In this pilot study, analysis will be descriptive throughout and hence no specific inferential hypotheses are being formally tested. We seek preliminary descriptive evidence that:

- Oral AZD4017 inhibits 11 $\beta$ -HSD1 activity in skin
- AZD4017 is safe and well-tolerated in patient with T2DM

- Oral AZD4017 regulates the skin function outcome measures described in this study
- Systemic GC levels and skin 11 $\beta$ -HSD1 activity, independently or in combination correlate with the skin function outcome measures described in this study

### 13.3. General statistical considerations

Unless otherwise specified, the last valid measurement before study medication administration will be utilized as the baseline value. In general, summary statistics [n (number of available measurements), arithmetic mean, standard deviation, median, minimum, and maximum] for quantitative variables and absolute and relative frequency tables for qualitative data will be presented.

Wherever possible the trial will be reported in accordance with the recommendations of the Consolidated Standards of Reporting Trials statement.

An initial blind review of the data will be completed prior to locking the database to identify patients to be excluded from per-protocol analysis.

### 13.4. Planned analyses

#### 13.4.1. Primary endpoint analysis

Skin 11 $\beta$ -HSD1 activity will be summarized descriptively in each treatment group at each time-point; the primary analysis will be on an intention-to-treat basis, will all patients included, as randomised. This will be supplemented by a per-protocol analysis that includes patients whose compliance with protocol is deemed satisfactory. Unadjusted and adjusted summaries (adjusted for gender, age and baseline HbA1c) for absolute values and changes from baseline will be presented; between-group differences in absolute values and changes from baseline will be presented together with 90% confidence intervals – deemed acceptable for pilot studies [65]. Adjusted summaries will be obtained via a linear regression model which mirrors analysis of covariance. Where necessary, transformations to a normal distribution will be performed. Preliminary proof-of-concept will be considered to have been achieved if adjusted mean 11 $\beta$ -HSD1 activity in skin at 28 days is lower in the active treatment arm compared to the placebo arm. Estimated sample sizes for future trials will be produced based on the pooled standard deviations from both treatment arms for the following outcomes: 11 $\beta$ -HSD1 activity in skin (at baseline and 28 days), sudomotor function, skin hydration, epidermal barrier function (at baseline and 35 days), integrity (at baseline and 28 days) and recovery (at baseline and 28 days – 3 hour, 2 day and 7 day), skin thickness (at baseline and 35 days) and wound healing (at baseline and 28 days – 2 day and 7 day). Sample sizes for a range of plausible and clinically-meaningful between-group differences will be presented, assuming analysis of covariance controlling for baseline values would be used. Correlation (Pearson's *r*) between baseline and follow-up values will be estimated in the combined treatment groups to aid in the sample size estimates. If the

correlation between the measurements at the two time-points is  $\rho$ , ANCOVA comparing groups of  $(1-\rho^2)n$  subjects has the same power as a t-test comparing groups of  $n$  subjects.

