## **3. STUDY ENDPOINTS**

### **3.1. Primary endpoint**

24 hour 11 $\beta$ -HSD1 activity in skin (efficacy) at baseline and day 28

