#### **13.4.2. Secondary endpoint analyses**

##### **13.4.2.1. Efficacy**

Systemic 11 $\beta$ -HSD1 activity and skin function analyses will be conducted as for the primary endpoint (above). The strength of association between skin AZD4017 at day 28 concentration and plasma AZD4017 at day 35 in the active treatment arm will be assessed using Pearson's product moment correlation coefficient; for severely skewed variables for which a suitable transformation cannot be found, Spearman rank correlation will be used. For all correlation analyses, absolute correlation coefficients with a value of  $r(ho) \geq 0.3$  will be considered preliminary evidence of substantive association.

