##### **13.4.2.2. Safety**

Safety analyses will be conducted in all patients who received any study treatment, according to treatment received. Continuous safety variables (BMI, waist-hip ratio, BP, HbA1c levels, lipids, FBC, LFT, eGFR, U+E, adrenal and thyroid function test) will be summarized descriptively by patient group at each timepoint. Unadjusted and adjusted summaries (adjusted for gender, age and baseline HbA1c) for absolute values and changes from baseline will be presented; between-group differences in absolute values and changes from baseline will be presented together with 90% confidence intervals. Adjusted summaries will be obtained via a linear regression model which mirrors analysis of covariance. Where necessary, transformations to a normal distribution will be performed. Where applicable, numbers of patients in each group whose values exceeded ULN (or were below the lower limit of normal) during the trial will be presented, corrected for exposure by 100 patient years.

Line listings of all AEs will be provided in the end of trial report. The frequency of all AE during the study period will be presented for each treatment group separately within classes of AEs defined by CTCAE preferred term. The data will be displayed as number of subjects experiencing the AE, percentage of subjects, and number of AE. AE will also be summarized by severity and relation to IMP. For recurrent AEs, the most severe occurrence will be recorded per AE per patient. AE data will also be corrected for exposure by 100 patient-years. For expected AEs the recorded rates will be compared against the rates outlined in the IB.

In addition to the above, the proportions of patients who passed the overall assessment of blood safety will be summarised using absolute and relative frequencies at each visit, in all patients and by treatment group at days 0, 7, 28, 35 & 42.

No inferential testing will be conducted; safety will be assessed in terms of the clinical relevance of the AEs reported and of any observed differences between groups.

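### The adjusted model behind proof-of-concept leaves out the outcome's own baseline, giving up precision that the same paragraph credits to ANCOVA

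*Protocol*

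**What the plan says.** - **Endpoint (3.1):** "24 hour 11 $\beta$ -HSD1 activity in skin (efficacy) at baseline and day 28". A baseline measurement is therefore planned.
- **Adjustment set (13.4.1):** "Unadjusted and adjusted summaries (adjusted for gender, age and baseline HbA1c) for absolute values and changes from baseline will be presented". The method follows: "Adjusted summaries will be obtained via a linear regression model which mirrors analysis of covariance". Between-group differences come with 90% confidence intervals.
- **Decision rule (13.4.1):** "Preliminary proof-of-concept will be considered to have been achieved if adjusted mean 11 $\beta$ -HSD1 activity in skin at 28 days is lower" on active treatment than on placebo. The deciding quantity is thus an adjusted absolute value at day 28, judged on its point estimate.
- **Next trial (13.4.1, same paragraph):** sample sizes will be produced "assuming analysis of covariance controlling for baseline values would be used". The baseline-to-follow-up correlation ρ will be estimated, and the paragraph notes that ANCOVA with (1−ρ²)n per group matches a t-test with n per group.
- **Reach:** 13.4.2.1 analyses systemic activity and skin function in the same way as the primary endpoint. Safety (13.4.2.2) does not refer back to 13.4.1. It repeats its own list: "adjusted for gender, age and baseline HbA1c".

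**The concern.** In a two-measurement design the outcome's own baseline is usually the strongest available predictor of follow-up. The protocol collects it and states what it is worth, but its closed covariate list omits it from this trial's model. Two things are at stake.

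The first is the width of the 90% intervals, which are the main product of a descriptive pilot.

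The second is the proof-of-concept estimate. Allocation (6.4.3) is simple 1:1, with no stratification described, and about 12 completers per arm are expected. A chance difference in baseline skin activity then passes in part into the day-28 difference, and the criterion has no margin to absorb it.

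The change-from-baseline summaries do not close the gap. They subtract the baseline with a slope fixed at 1, and they are not the quantity on which proof-of-concept is judged.

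**Working it through.** **Inputs.** There are 12 completers per arm (13.9), two-sided 90% intervals (13.4.1), and three covariates plus treatment in the planned model. ρ is not in the documents, so it is assumed at 0.3, 0.5 and 0.7.

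**The plan's own figures.** 12/(1−0.20) = 15 per arm, as stated in 13.9. The (1−ρ²) rule also checks. For n = 100 per group and a difference of 0.4 SD, t-test power is 0.8074. ANCOVA with 100(1−ρ²) per group gives 0.8074 at every ρ tried from 0.3 to 0.8.

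**Relative variance of the day-28 difference**, with equal variances at both times and a common slope, ignoring any contribution from the three listed covariates:
- absolute value without own baseline: 1
- change score: 2(1−ρ)
- own baseline in the model: 1−ρ²

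**90% half-width in SD units** = t × √(relative variance) × √(2/12). Degrees of freedom are 24−5 = 19 (t = 1.729) without the baseline and 24−6 = 18 (t = 1.734) with it.

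| ρ | absolute | change score | own baseline added | variance cut | equivalent n per arm, 12/(1−ρ²) |
|---|---|---|---|---|---|
| 0.3 | 0.71 | 0.84 | 0.68 | 9% | 13.2 |
| 0.5 | 0.71 | 0.71 | 0.61 | 25% | 16.0 |
| 0.7 | 0.71 | 0.55 | 0.51 | 51% | 23.5 |

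The change score is noisier than the absolute comparison when ρ < 0.5. Its variance is 2/(1+ρ) times that of the baseline-adjusted model, so at this level it is never the better of the two.

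**Small-sample check.** Simulated regressions at 12 per arm (4,000 replicates) gave mean half-widths, without and with the baseline, of 0.748 and 0.736 (ρ 0.3), 0.751 and 0.671 (ρ 0.5), and 0.752 and 0.554 (ρ 0.7). Squaring the ratios gives net cuts of about 3%, 20% and 46%. At ρ = 0 the baseline widens the interval slightly, from 0.751 to 0.773.

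**Unequal spread.** The only before-and-after figures in the protocol are urinary (5.3): 0.99+0.27 falling to 0.11+0.06. If the second numbers are SDs and skin behaves likewise on the raw scale (both assumptions), the active-arm day-28 SD is k = 0.06/0.27 = 0.222 of its baseline value. With a common slope b = ρ(1+k)/2, the proportional cut is ρ²(1+k)²/[2(1+k²)] = ρ² × 1.494/2.099 = 0.712ρ². That is 6%, 18% and 35%. Simulation at 12 per arm gave about 13% at ρ 0.5, 31% at ρ 0.7 and at most about 2% at ρ 0.3.

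**Chance imbalance.** The baseline difference between arms has standard error √(2/12) = 0.41 SD. An imbalance above 0.5 SD in either direction occurs about 22% of the time (normal approximation). On average a fraction ρ of it passes into the day-28 difference.

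**Decision rule.** For an assumed true effect of 0.5 SD, the chance that the point estimate favours active treatment is Φ(0.5/0.408) = 0.89 without the baseline. With it, the chance is 0.92 at ρ 0.5 and 0.96 at ρ 0.7. With no true effect it is 0.50 either way.

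**The case against.** The best counter-argument is that the wording leaves room. The model is said to resemble analysis of covariance, the paragraph elsewhere uses that term for baseline control, and the analysis plan is to be finalised before unblinding (13.10). This supports asking for clarification, but it does not override an explicit list that omits the covariate.

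It is also fair that the analysis is descriptive (13.2), that baseline balance will be reported (4.2), and that the effect on meeting the criterion is modest. If skin inhibition approaches the roughly 90% that 5.3 suggests for 400 mg twice daily, the criterion would probably be met with either model. The gain would then lie mainly in interval width and in the skin-function outcomes. The percentages also rest on an assumed ρ and on equal variances. Strictly, ρ should be the correlation left after the three listed covariates. All of this limits the size of the point, not its direction.

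Three stronger readings are tempting and not supported:
- **That the pilot cannot supply the ANCOVA residual SD for its successor.** 13.4.1 plans pooled SDs at both times and Pearson's r, and these give it through the (1−ρ²) rule.
- **That baseline is ignored altogether.** Change-from-baseline differences stand beside the absolute ones.
- **That every patient will have a usable baseline.** The biopsy needs separate consent (6.4.2), 11.10 provides for radioassay failure, and missing data are a feasibility endpoint (13.7). Under available-case analysis, a patient without a baseline value would leave the new model but not the planned day-28 one.

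**Conclusion.** The point holds as an avoidable loss of precision in the model that carries the proof-of-concept decision. A reader might infer bias, but randomisation rules that out, and there is no formal test to invalidate. With equal variances and a common slope, the variance of the day-28 difference falls by about 9%, 25% or 51% at ρ 0.3, 0.5 or 0.7. Net of small-sample cost at 12 per arm, the simulated cuts are about 3%, 20% and 46%. They are lower again if active treatment compresses the day-28 spread. At ρ of about 0.3 or less the benefit is slight. At 0.5 or more it is worth several patients per arm in a trial of 30. ρ is an assumption throughout. The inconsistency inside 13.4.1 needs resolving whatever its value.

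**What to change.** In 13.4.1, insert 'the baseline value of the same outcome' ahead of the three listed covariates, and state that this model supplies the adjusted day-28 mean for proof-of-concept. Section 13.4.2.1 then inherits the change.

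Limit it to outcomes with a pre-dose baseline. Wound healing and the 48-hour and 7-day barrier-recovery readings are excluded, because their Visit 1 series is read after dosing has begun.

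Edit the separate list in 13.4.2.2 in the same way, entering baseline HbA1c only once when HbA1c is the outcome.

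With the own baseline in the model, the adjusted treatment difference is the same for absolute values and for changes on the same scale. The two presentations can then no longer disagree.

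The cost is one degree of freedom (19 to 18 with 24 completers, t from 1.729 to 1.734), a slightly wider interval if ρ is near zero, and, under available-case analysis, the loss of patients with a missing baseline unless that value is imputed. The change can be made before unblinding without harm to the trial.
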